# Intravenous iron isomaltoside 1000 administered by high single-dose infusions or standard medical care for the treatment of fatigue in women after postpartum haemorrhage: study protocol for a randomised controlled trial

**DOI:** 10.1186/1745-6215-16-5

**Published:** 2015-01-14

**Keywords:** Postpartum haemorrhage, Iron deficiency, Intravenous iron, Postpartum fatigue

## Abstract

**Background:**

Postpartum haemorrhage can lead to iron deficiency with and without anaemia, the clinical consequences of which include physical fatigue. Although oral iron is the standard treatment, it is often associated with gastrointestinal side effects and poor compliance. To date, no published randomised controlled studies have compared the clinical efficacy and safety of standard medical care with intravenous administration of iron supplementation after postpartum haemorrhage.

The primary objective of this study is to compare the efficacy of an intravenous high single-dose of iron isomaltoside 1000 with standard medical care on physical fatigue in women with postpartum haemorrhage.

**Methods/Design:**

In a single centre, open-labelled, randomised trial, women with postpartum haemorrhage exceeding 700 mL will be allocated to either a single dose of 1,200 mg of iron isomaltoside 1000 or standard medical care. Healthy parturients with a singleton pregnancy will be included within 48 hours after delivery.

Participants will complete structured questionnaires that focus on several dimensions of fatigue and mental health (Multidimensional Fatigue Inventory, Edinburgh Postnatal Depression Scale and the Postpartum Questionnaire), at inclusion and at follow-up visits after three days, one week, three weeks, eight weeks, and 12 weeks postpartum. The primary endpoint is the aggregated change in physical fatigue score within 12 weeks postpartum, as measured by a subscale of the Multidimensional Fatigue Inventory. The primary objective will be considered to have been met if an intravenous high single dose of iron isomaltoside 1000 is shown to be superior to standard medical care in women after postpartum haemorrhage regarding physical fatigue.

For claiming superiority, we set the minimal clinically relevant difference between the mean scores at 1.8, and the assumed standard deviation at 4.2. Hence, 87 participants per treatment group are needed in order to demonstrate superiority; to provide an extra margin for missing data and dropouts, 200 women will be included.

**Discussion:**

The study will provide evidence on relevant clinical outcomes beyond biochemical parameters for intravenous iron isomaltoside 1000 compared to standard medical care in women after postpartum haemorrhage.

**Trial registration:**

This trial is registered with Clinicaltrials.gov (identifier: NCT01895218) on 26 June 2013.

**Electronic supplementary material:**

The online version of this article (doi:10.1186/1745-6215-16-5) contains supplementary material, which is available to authorized users.

## Background

### Postpartum iron deficiency and anaemia

Blood loss of up to 500 mL at delivery is considered to be a normal physiological mechanism that brings a woman’s haemoglobin value back to the pre-pregnancy level [1, 2]. Severe postpartum haemorrhage (PPH) is defined as blood loss above 1,000 mL within the first 24 hours after delivery [3]. Full body iron stores can replete blood loss up to a maximum of 1,000 mL [4], which means that many women with a blood loss between 500 and 1,000 mL will develop iron deficiency with or without anaemia. Therefore, in the present study of iron supplementation, we considered ≥700 mL blood loss to be the appropriate clinically significant criteria for inclusion.

Postpartum iron deficiency anaemia may lead to several clinical consequences, the most prominent of which is maternal physical fatigue [5]. It is currently unknown whether treatment can help this fatigue or whether biochemical markers, such as haemoglobin (Hb), ferritin and other biomarkers, can measure the condition and predict clinical treatment effects.

Breastfeeding is important for the health of the infant. Delayed onset of postpartum lactogenesis increases the risk of inadequate infant growth and early discontinuation of breastfeeding [6, 7]. A retrospective Canadian study found postpartum iron deficiency anaemia to be negatively associated with the duration of breastfeeding [8], but it is unknown whether postpartum iron deficiency anaemia is associated with delayed postpartum lactogenesis, or if the duration of breastfeeding can be improved with iron treatment after delivery.

The clinical consequences of postpartum iron deficiency without anaemia are not known in detail. However, iron deficiency without anaemia in women of childbearing age is associated with fatigue, impaired physical work performance, deficient cognitive functions and mood disturbances [9]. Therefore, it is possible that postpartum iron deficiency without anaemia contributes significantly to physical fatigue in the puerperium, and that iron treatment is beneficial for these women and their infants.

### Intravenous iron

The currently available intravenous iron preparations are generally considered equally efficacious but vary in terms of molecular size, kinetics, bioavailability and toxicology [10, 11]. The European Medicines Agency recently reviewed the safety of intravenous iron. It concluded that the benefits of intravenous iron are greater than their risks and was unable to establish a difference in the safety profiles of the products [12].

Isomaltoside 1000, the carbohydrate component in iron isomaltoside 1000 (Monofer®), has a mean molecular weight of 1,000 Da and consists predominantly of three to five glucose units. The carbohydrate isomaltoside is linear and unbranched with a low immunogenic potential. Iron isomaltoside 1000 has strongly bound iron within the iron isomaltoside formulation, which enables a controlled slow release of bioavailable iron to the iron-binding proteins with minimal risk of free iron toxicity [13].

To date, iron isomaltoside 1000 has been approved in Europe for the treatment of iron deficiency anaemia. The indications are when oral iron preparations are ineffective or cannot be used, or where there is a clinical need to deliver iron rapidly. Several studies of iron isomaltoside 1000 treatment of iron deficiency anaemia have been published, including the use of bolus injections and high single-dose infusions, without detected unexpected safety issues [14–17].

Iron isomaltoside 1000 was chosen for this study as it is approved for high single dosing of up to 20 mg/kg. The high single dose is preferable in the treatment of puerperal women, as they need fast correction of their iron deficit before leaving the hospital.

### Previous studies and current guidelines

International guidelines are available for the treatment of iron deficiency anaemia in pregnancy and the postpartum period [18–21]. These guidelines recommend oral iron supplementation in mild anaemia, intravenous iron in moderate anaemia and when oral iron supplementation is not tolerated, and allogeneic red blood cell (RBC) transfusion in severe and symptomatic cases. These guidelines do not deal with screening for or treatment of iron deficiency without anaemia.

Denmark has no published national guideline on the screening or treatment of postpartum iron deficiency with or without anaemia. In clinical practice, doctors usually recommend oral iron supplementation to parturients with PPH, and RBC transfusion to those with severe symptoms of anaemia. Since puerperal women with a Hb level of ≤6.5 g/dL (4.0 mmol/L) often have severe symptoms of anaemia, we will not include these parturients in the study.

No prospective randomised clinical studies have yet assessed the effect of intravenous iron supplementation in comparison to standard medical care in women after PPH with a clinical outcome as the primary endpoint. There have been 10 randomised controlled studies that have compared intravenous iron to oral iron supplementation in women with diagnosed postpartum iron deficiency anaemia [22–31]. The inclusion criteria of these studies were Hb concentration up to 10 days after delivery, and the primary study endpoints were Hb concentration, iron parameters and comparisons thereof. Generally, these studies have demonstrated improvement of Hb and iron parameters, favouring intravenous iron. With regard to safety, oral iron was associated with gastrointestinal side effects in up to 30% of the participants, with a compliance rate as low as 50%. These findings must be balanced against the very low risk of severe hypersensitivity reactions with intravenous iron [12].

Hb concentration and other biochemical parameters are influenced by the haemodynamic changes, and are therefore considered unreliable for diagnosing iron deficiency anaemia in the first week(s) after giving birth [32]. However, it is crucial that these women can benefit from treatment in the clinically important first days after delivery. In the present study, we have chosen to include women based on their clinically estimated blood loss after delivery, and we hypothesise that women with clinically significant PPH will have an increased risk of developing iron deficiency with or without anaemia.

We believe that iron treatment should be administered in order to improve clinical symptoms of iron deficiency with or without anaemia, not just to improve biochemical markers. This is in accordance with a systematic review, which concluded that there is a lack of high-quality studies with clinical outcomes [33]. Therefore, we have decided that the primary outcome in the present study will be a clinically significant improvement in the physical fatigue score between the treatment groups. We hypothesise that intravenous iron is superior to standard medical care.

### Objective

The primary objective of this study is to compare the efficacy of intravenous high single doses of iron isomaltoside 1000 to standard medical care on physical fatigue in women with PPH.

## Methods/Design

### Study design

The study will be a randomised, comparative, open-label single-centre study with a 1:1 allocation ratio. The trial is a company-sponsored interventional trial conducted according to International Conference on Harmonization-Good Clinical Practice (ICH-GCP) guidelines [34].

### Inclusion criteria

Women, regardless of mode of delivery, will be eligible for inclusion in the study if they fulfil the following criteria: (1) they have signed the informed consent form, and (2) they have either (a) PPH ≥700 and ≤1,000 mL or (b) PPH >1,000 mL and Hb >6.5 g/dL (4.0 mmol/L) measured at >12 hours after delivery (Figure 1).

**Figure 1 Fig1:**
[figure not shown]
**Trial flow.** Women with postpartum haemorrhage ≥700 and ≤1,000 mL or PPH >1,000 mL and haemoglobin >6.5 g/dL (4.0 mmol/L) within 48 hours of delivery will be screened for inclusion and exclusion and asked for consent to participate. Baseline questionnaires are completed and blood samples are taken. The participants are randomised to either intravenous iron isomaltoside 1000 or standard medical care. Follow-up visits with completion of questionnaires, blood samples and maternal milk samples are performed at three days, and one, three, eight and 12 weeks after intervention. (EPDS: Edinburgh Postnatal Depression Scale; Hb: haemoglobin; HELLP: haemolysis, elevated liver enzymes, and low platelet count; MFI: Multidimensional Fatigue Inventory; PPH: postpartum haemorrhage; PPQ: Postpartum Questionnaire; RBC: red blood cells; subMFI: subscale of the Multidimensional Fatigue Inventory; subPPQ: subscale of the Postpartum Questionnaire).

### Exclusion criteria

Exclusion criteria: age <18 years; multiple births; peripartum RBC transfusion; known iron overload or disturbances in the utilisation of iron (such as haemochromatosis or haemosiderosis); known hypersensitivity to parenteral iron or any excipients in the investigational drug products; a history of active asthma within the previous five years; a history of multiple allergies; known decompensated liver cirrhosis or active hepatitis; haemolysis, elevated liver enzymes, and low platelet count (HELLP) syndrome; active acute infection (clinical symptoms or fever above 38.5°C); rheumatoid arthritis; history of anaemia caused by a known haematological disorder other than iron deficiency; inability to read, speak and understand the Danish language; participation in any other clinical study where the study drug has not passed five half-lives prior to the baseline and any other medical condition that, in the opinion of the investigator, may cause the parturient to be unsuitable for completion of the study or place her at potential risk from participating in the study.

### Randomisation

Participants will be randomised using an interactive web response system (eClinical OS™, Merge Healthcare, Morrisville, NC, United States). The randomisation lists will be prepared centrally by the contract research organization BioStata ApS, Birkerød, Denmark using a validated computer program. The randomisation will be stratified by bleeding volume (PPH: 700 to 1,000 mL or PPH >1,000 mL). Within each bleeding category, there will be a 1:1 randomisation ratio to one of the two treatment groups.

### Intervention

The participants will be randomised to either standard medical care or iron isomaltoside 1000. Standard medical care (current treatment practice) at the Department of Obstetrics, Copenhagen University Hospital, Rigshospitalet is typically to recommend women with PPH to either continue oral iron supplementation, as during pregnancy (the Danish Health and Medicines Authority recommends 40 to 50 mg oral iron supplementation daily [35]), or to take 100 mg oral iron one or two times daily for a variable time period. The actual use of iron supplementation, including specific preparation, dose and duration of treatment, will be monitored at each follow-up visit.

Immediately after acute bleeding such as PPH, the Hb level is inaccurate for calculating individual dosing of iron supplementation. Hence, the iron isomaltoside 1000 fixed dosage in this study is based on the expected iron deficiency in women after PPH. Body iron stores are approximately 500 to 750 mg and the average iron loss through PPH is approximately 500 mg, as 500 mL blood loss equals 250 mg iron loss [4]. In previous studies of women with postpartum anaemia, oral iron treatment dosages were 130 to 200 mg per day over a period of 42 to 84 days, resulting in a total average dose of 11.088 mg [23–27]. The intestinal iron absorption varies considerably but is believed to be a maximum of 10% [36], resulting in a total expected absorption of 1,100 to 1,200 mg. Thus, the cumulated iron dosages in these studies are in accordance with the chosen treatment dose in this study.

In the group allocated to iron isomaltoside 1000, Pharmacosmos A/S, Holbaek, Denmark, the iron replacement dose is set to 1,200 mg. The dose is diluted in 100 mL 0.9% sodium chloride, Fresenius Kabi AG, Bad Homburg, Germany, and administered over a period of approximately 15 minutes. No test dose is applied. Participants with a pre-pregnancy weight <45 kg will receive a reduced single dose of 1,000 mg iron isomaltoside 1000, administered in the same fashion. In both treatment groups, participants may be given a ‘rescue’ allogeneic RBC transfusion if this procedure is clinically indicated.

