### Setting, location and follow-up

The parturients will be screened for inclusion in the study over an 18-month period at the Department of Obstetrics, Copenhagen University Hospital, Rigshospitalet, a tertiary hospital that performs between 6,000 and 7,000 deliveries per year. Eligible parturients are informed about the study and must provide their written consent within 48 hours after delivery. The duration for each individual participant is approximately 12 weeks and involves five follow-up visits by a midwife at the participant’s home. The timeframes of the follow-up visits are three days (between two and four days), one week (between six and eight days), three weeks (between 19 and 23 days), eight weeks (between seven and nine weeks) and 12 weeks (between 11 and 13 weeks).

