### Outcomes and safety measures

The primary outcome is the aggregated change in physical fatigue score within 12 weeks postpartum, as measured by a subscale of the Multidimensional Fatigue Inventory (MFI) [37]. Secondary efficacy outcomes include changes in the Hb concentration, *p-*ferritin, *p-*iron, *p-*transferrin, transferrin saturation, reticulocyte count, mean reticulocyte Hb content, other MFI and Postpartum Questionnaire (PPQ) fatigue items, symptoms of postpartum depression, time of postpartum lactogenesis, time of discontinuation of breastfeeding and transfusion of allogeneic RBCs.

The safety outcomes are discontinuation due to intolerance, frequency, nature and severity of adverse events, vital signs, and *p*-sodium, *p-*potassium, *p-*calcium, *p-*phosphate, *p-*urea, *p-*creatinine, *p-*albumin, *p*-bilirubin, *p*-aspartate aminotransferase and *p*-alanine aminotransferase levels. Other outcomes are maternal milk iron level, anaemia symptoms and gastrointestinal symptoms.

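### The weight rule for the single iron dose (1,200 mg from 45 kg pre-pregnancy weight, 1,000 mg below) does not ensure the 20 mg/kg maximum cited as the reason for choosing the product

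*Protocol article*

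**What the plan says.** Background, Intravenous iron, gives the reason for selecting the product: "it is approved for high single dosing of up to 20 mg/kg". This is the only per-kilogram maximum in the article, and the weight it refers to (pre-pregnancy or current) is not named.

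Methods/Design, Intervention, fixes the dose: "the iron replacement dose is set to 1,200 mg", "administered over a period of approximately 15 minutes". It is therefore one administration, and all of it counts against a single-dose maximum. The only adjustment for weight is: "Participants with a pre-pregnancy weight <45 kg will receive a reduced single dose of 1,000 mg iron isomaltoside 1000". The amount is justified by the expected iron deficit and by a comparison with earlier oral-iron trials, "resulting in a total expected absorption of 1,100 to 1,200 mg". No reason is given for the 45 kg cut-off.

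The exclusion list, which begins "age <18 years; multiple births; peripartum RBC transfusion", has no weight criterion. Its closing clause on investigator judgement concerns medical conditions, not dose per kilogram. On timing, Setting, location and follow-up says that women "must provide their written consent within 48 hours after delivery". Consent and ethical considerations records ethics and regulatory approval of the study without mentioning dose per kilogram.

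**The concern.** The article states a maximum, two doses and a cut-off, and these do not fit together. A maximum of 20 mg/kg implies a minimum weight for each fixed dose, and both minimum weights lie above the weights at which the rule starts to give those doses. Followed as written, the rule can give a light woman a single intravenous dose above the maximum cited for the product.

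What is at stake is mainly participant safety, and secondly the description of the safety results. The outcomes include "discontinuation due to intolerance, frequency, nature and severity of adverse events". These would pool women dosed within the approved maximum with women dosed above it, and a reader of the Background section could suppose that all were within it.

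**Working it through.** **Inputs.** Maximum single dose 20 mg/kg (Background, Intravenous iron). Doses of 1,200 mg and 1,000 mg, with the cut-off at 45 kg pre-pregnancy weight (Intervention). Retained pregnancy weight is not in the article; the values of 5, 8, 12 and 15 kg below are assumptions that show the range.

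**Step 1: the plan's own dose figure.** The Intervention section prints an average oral total of 11.088 mg. This must mean 11,088 mg, because the quoted regimens run from 130 × 42 = 5,460 mg to 200 × 84 = 16,800 mg. At 10% absorption, 11,088 × 0.10 = 1,109 mg, inside the stated 1,100 to 1,200 mg. The fixed dose is thus explained by iron deficit. The derivation contains no body weight and does not lead to a 45 kg cut-off.

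**Step 2: minimum weight for each dose.** Minimum weight = dose / 20.
- 1,200 / 20 = 60 kg, whereas the rule gives 1,200 mg from 45 kg.
- 1,000 / 20 = 50 kg, whereas the rule gives 1,000 mg only below 45 kg.

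**Step 3: dose per kilogram on pre-pregnancy weight.**

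| Pre-pregnancy weight | Dose | mg/kg | Dose at 20 mg/kg | Excess |
|---|---|---|---|---|
| 40 kg | 1,000 mg | 25.0 | 800 mg | 200 mg |
| 44 kg | 1,000 mg | 22.7 | 880 mg | 120 mg |
| 45 kg | 1,200 mg | 26.7 | 900 mg | 300 mg |
| 50 kg | 1,200 mg | 24.0 | 1,000 mg | 200 mg |
| 55 kg | 1,200 mg | 21.8 | 1,100 mg | 100 mg |
| 60 kg | 1,200 mg | 20.0 | 1,200 mg | 0 mg |

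At 45 kg the excess is 300 / 900 = 33%. Below 45 kg the dose always exceeds 1,000 / 45 = 22.2 mg/kg.

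**Step 4: dose per kilogram on weight at dosing.** With pre-pregnancy weight w and retained weight r, 1,200 mg complies when r ≥ 60 − w: 15 kg at w = 45, 10 kg at w = 50, 5 kg at w = 55. The 1,000 mg dose complies when r ≥ 50 − w: 6 kg at w = 44, 10 kg at w = 40.

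For a woman of 45 kg before pregnancy, mg/kg = 1,200 / (45 + r) and excess = 1,200 − 20 × (45 + r). The last column is the pre-pregnancy range in which 1,200 mg exceeds the maximum, 45 to under 60 − r.

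| Retained weight (assumed) | mg/kg at w = 45 | Excess at w = 45 | Range over the maximum |
|---|---|---|---|
| 5 kg | 24.0 | 200 mg | 45 to <55 kg |
| 8 kg | 22.6 | 140 mg | 45 to <52 kg |
| 12 kg | 21.1 | 60 mg | 45 to <48 kg |
| 15 kg | 20.0 | 0 mg | none |

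**The case against.** The strongest reply is that no promise is broken. The 20 mg/kg figure is given as a property of the product and a reason for choosing it. The article does not say that each participant will be kept within it, and it presents the dose as fixed by iron deficit. Nor is the trial confined to labelled use: the approved indication is iron deficiency anaemia, while women are enrolled on blood loss. A reader might infer that the protocol violates a commitment of its own, or that the regulator did not agree to the dose. The documents support neither. What stands against this reply is that the figure is cited in favour of the product while the rule does not hold the dose to it, and that nothing in the article says an excess was intended.

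The second reply concerns the weight basis. If the maximum refers to weight at dosing, the size of the problem depends on a quantity the article does not give, and 26.7 mg/kg is the extreme case of no retained weight. At 15 kg retained, the 45 kg cut-off fits exactly and the 1,000 mg dose complies from 50 − 15 = 35 kg. The rule may have been built on such an allowance, but that is inference. This reply stands as a limit on the size. It does not remove the point, because any retention below 15 kg leaves women near 45 kg above the maximum. Dosing also comes after the delivery and after a blood loss of at least 700 mL.

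A third reply is that a journal article condenses the full protocol. The weight basis and the reason for the cut-off may well be given there. But both doses and the cut-off are stated here as rules, so the mismatch is in what the article fixes.

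Finally, nothing in the article says that doses moderately above 20 mg/kg cause harm, and the comparison of adverse events between the arms as assigned remains valid. Both are correct. The safety results still describe the regimen; they just cannot be presented as results for dosing within the approved maximum throughout.

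**Conclusion.** The point holds in a limited form: the weight rule does not ensure the 20 mg/kg single-dose maximum.

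On pre-pregnancy weight, the excess covers all women below 60 kg, both those given 1,200 mg and those given 1,000 mg. On weight at dosing, the affected range narrows as retained weight rises, and for the 1,200 mg dose it closes at 15 kg retained.

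The conclusion rests on reading the whole infusion as one single dose and on the absence of any further cap in the full protocol, which is not shown. The article gives no weight distribution, so the number of women affected cannot be calculated and may be small. It would be wrong to infer that women in general were dosed at 26.7 mg/kg, or that the power calculation or the fatigue analysis is compromised; neither depends on dose per kilogram.

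**What to change.** **For any woman still to be dosed:** weigh her before the infusion and give min(1,200 mg, 20 mg/kg × body weight at dosing). That is 1,200 mg from 60 kg, 1,100 mg at 55 kg, 1,000 mg at 50 kg and 900 mg at 45 kg. A continuous cap removes only the excess, whereas a drop to 1,000 mg for everyone under 60 kg would take 200 mg from a woman of 57 kg whose excess is 60 mg.

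The cost is one weighing, a dosing amendment and a lower dose for women under 60 kg at dosing. Below 50 kg the dose falls under 1,000 mg, which is less than any dose the protocol now gives and below the 1,100 to 1,200 mg on which the fixed dose is based. A mid-trial change would also leave two dosing regimens among light women in the iron arm, which must be reported. If exceeding 20 mg/kg was intended, say so and give the reason.

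**If recruitment is complete**, which is likely since Trial status expected this in August 2014 and the article appeared in January 2015: report the mg/kg received in the iron arm on a stated weight basis, with the number of women above 20 mg/kg. Pre-pregnancy weight is needed to assign the dose and should be available; add weight at dosing if it was recorded. Do not describe the regimen as within the approved maximum for all participants.

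Any split of adverse events at 20 mg/kg should be labelled descriptive. In an iron arm of about 200 / 2 = 100 women it would be imprecise, and with a nearly fixed dose it is essentially a split by body weight, so it cannot separate the two. The cost is a sentence and a short table.
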